### Data analysis

The following data analysis plan will be implemented in both the UK and US emulated trials.

#### Notation

Let A denote an indicator variable for treatment strategy (A=0 indicates no prescription of azithromycin and A=1 indicates prescription of azithromycin). Let $Y_{t}\left(0\right)$ denote the potential outcome under treatment A=0 at time t,t∈{0,1} where t=1 is 12 months after t=0. Similarly, let $Y_{t}\left(1\right)$ denote the potential outcome under treatment A=1 at time t. Finally, C denotes the confounding factors listed in the section titled "Covariates" and in figure 2. In the following sections, we describe the causal estimand of interest, the main analysis plan with a focus on the primary outcome, and the key differences in the analyis plan for the secondary outcomes.

#### Causal estimand of interest

The target trial reported the difference in mean changes (between month 0 and month 12) in FEV_1_% between treatment groups in the total population:

(1)
$$ATE=E\{Y_{1}(1)-Y_{0}(1)\}-E\{Y_{1}(0)-Y_{0}(0)\}$$

where the expectations refer to the population of individuals meeting the criteria for the target trial. This is equivalent to the difference in means at the end of follow-up as the observed value of Y at time 0 is unaffected by treatment, that is, $Y_{0}\left(a\right)=Y_{0},i.e.$

(2)
$$ATE=E\{Y_{1}(1)\}-E\{Y_{1}(0)\}$$

Our causal estimand is interpreted as the expected difference in FEV_1_% at month 12 if everyone had taken azithromycin for 12 months, compared with a scenario where no one took azithromycin for 12 months.

#### Main analysis

In the target trial, the authors investigated the change in FEV_1_% from baseline, with adjustment for baseline FEV_1_%. This is equivalent to a regression of the mean FEV_1_% at follow-up with adjustment for baseline FEV_1_%. We note that in the absence of imbalance between treatment groups in baseline FEV_1_%, the adjustment of baseline FEV_1_% is not required but may result in gains in efficiency. Both approaches result in estimates of the ATE as defined in equations(1)  (2).

In the emulated trials, we need to account for differences between treatment groups at baseline, including baseline FEV_1_%. We also require assumptions of positivity, no interference, consistency and conditional exchangeability (conditional on C). We use augmented inverse-probability-of-treatment weighting (AIPTW) to control for potential confounding by C. AIPTW involves defining models for the treatment and outcome. This approach was chosen as it is doubly robust, meaning that it gives consistent estimates of treatment effects if either the treatment model or outcome model is correctly specified.^27^ This represents an advantage compared with the alternative propensity score or outcome-regression based approaches which are singly robust.

The first step in implementing AIPTW is to estimate the propensity scores, that is, the probability of treatment conditional on baseline covariates:

(3)
PS=P(A=1|C)

Propensity scores will be estimated using logistic regression, including C as linear terms.

In the second step, we specify an outcome model conditional on treatment and covariates:

(4)
$$Y_{1}=\gamma_{0}+\gamma_{A}A+\gamma_{C}C+\varepsilon$$

The AIPTW estimator for

(5)
$$\hat{E}[Y_{1}(a)]=\frac{1}{n}\sum_{i=1}^{n}\left\{\frac{I(A_{i}=a)Y_{1i}}{\hat{P}(A_{i}=a|C_{i})}-\frac{I(A_{i}=a_{i})-\hat{P}(A_{i}=a|C_{i})}{\hat{P}(A_{i}=a|C_{i})}\hat{E}(Y_{1i}|A_{i}=a,C_{i})\right\}$$

where $\hat{P}(A_{i}=a_{i}|C_{i})$ can be obtained using predictions from the propensity score model. The estimator in equation 5 can be used to estimate $E\left[Y_{1}\left(0\right)\right]$ and $E[Y_{1}(1)],$ and the difference between these two expectations is an estimate of the average treatment effect in the population. Standard errors can be obtained based on the efficient influence function.^28^

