**Figure 2 F2:**
[figure not shown]
Directed acyclic graph depicting assumed confounding relationships for the association between azithromycin at time 0 (azithromycin0) and FEV1% at time 1 (FEV1%1). U represents any unmeasured confounders. Subscripts denote time; 0* indicates prebaseline. BMI, body mass index; CFRD, cystic fibrosis-related diabetes; FEV_1_, forced expiratory volume in 1 s; NTM, nontuberculous mycobacteria; ppFEV_1_, per cent predicted FEV1.

Age, FEV_1_% and BMI z-score are continuous. Rate of decline in FEV_1_% is calculated as the difference between the absolute FEV_1_% measured at the index visit and the prior visit. Data on treatment prescription, the presence of infections, CFRD diagnosis, pancreatic insufficiency and non-intravenous hospital admissions will be binary indicators. Indicators for pancreatic insufficiency and non-intravenous hospital admissions are created using existing variables in the data. Registry data provide dates for treatment with intravenous antibiotics (at home or hospital). These data will be used to create a variable indicating the number of days on intravenous antibiotics since the last annual review (including treatment administered at home and hospital). Intravenous days will then be treated as a categorical variable with four categories: 0, 1–14, 15–28, 28+.

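### Both AIPTW working models are fixed as linear main effects of the same confounders, so a continuous confounder that acts non-linearly on both prescribing and outcome misspecifies both and double robustness gives no protection

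*Protocol article*

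**What the plan says.** Under Main analysis, the protocol article selects AIPTW for its double robustness: "it gives consistent estimates of treatment effects if either the treatment model or outcome model is correctly specified". It then fixes both working models.

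- Treatment model (equation 3): "Propensity scores will be estimated using logistic regression, including C as linear terms".
- Outcome model (equation 4): "Y_{1}=\gamma_{0}+\gamma_{A}A+\gamma_{C}C" plus an error term. Treatment and confounders enter additively, with no treatment-by-confounder term.

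Both use one set C, defined under Notation. Under Covariates, the protocol says how each confounder is coded:

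- "Age, FEV_1_% and BMI z-score are continuous".
- Decline, being a change between two visits, is effectively continuous too: "Rate of decline in FEV_1_% is calculated as the difference between the absolute FEV_1_% measured at the index visit and the prior visit".
- For one confounder linearity is already avoided: "Intravenous days will then be treated as a categorical variable with four categories: 0, 1–14, 15–28, 28" or more.
- Infections, treatments and diagnoses are indicators: "CFRD diagnosis, pancreatic insufficiency and non-intravenous hospital admissions will be binary indicators".

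The additional UK analysis (equation 6) adds only time and a time-by-treatment term. Under Secondary outcomes, FVC% and BMI z-score follow the same approach. Diagnostics plans standardised mean differences in the weighted sample, but states no rule for re-specifying either model.

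**The concern.** Double robustness is worth most when the two models are unlikely to fail for the same reason. Here both are held to straight lines in the same four continuous variables. The Covariates section says that prescribing follows clinical indication and that many of its drivers also relate to outcome. It is therefore plausible that, over ages 6 to 21 and FEV1% above 40, prescribing and later lung function both bend in the same variable. If so, neither model is right and confounding by that variable is only partly removed.

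This is a functional form that the protocol states, not a detail left unstated. More data do not shrink the bias, while the standard error does shrink, so confidence-interval coverage gets worse in the large samples that the protocol expects. The comparison with the target trial uses statistical significance and a 1.96 threshold, which both depend on the estimate and its standard error.

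**Working it through.** The protocol gives no figure on this point, so there is none to reproduce. The check is algebra plus simulation. All curvature, sample sizes and effect sizes below are assumptions.

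**1. When bias arises.** Write π and m for the true treatment probability and outcome mean given C, and π* and m* for the fitted working models. Taking expectations in equation 5 gives

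bias in E[Y1(a)] = E[ (π − π*)(m − m*) / π* ].

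This is a product of two errors. It is zero if either model is right, and generally non-zero if both are wrong in the same variable.

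**2. Simulation with quadratic curvature.** Assumed: n = 4000, one standard-normal and one binary confounder, true effect 2 points, residual SD 8, 300 replicates, working models as in equations 3 and 4. Monte Carlo error is about 0.02.

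| Truth | Bias |
|---|---|
| Both models linear | -0.02 |
| Outcome curved, treatment linear | -0.02 |
| Treatment curved, outcome linear | -0.01 |
| Treatment-by-confounder effect omitted, treatment linear | 0.00 |
| Outcome curved and interaction omitted, treatment linear | 0.01 |
| Treatment curved, interaction omitted | -0.32 |
| Both curved | -1.38 |
| Both curved, interaction omitted | -1.69 |
| Last case, quadratic in both models and outcome fitted by arm | 0.02 |

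The strongest curvature was 0.3 on the log-odds and -2 points per squared SD. At 2 SD from the mean that is 0.3 × 4 = 1.2 on the log-odds and -2 × 4 = -8 points. Over a grid starting at 0.1 and -0.5 (0.4 and -2 points at 2 SD), the bias ran from -0.10 to -1.35. Those two cells used 150 replicates, so the standard deviations of the estimate are about 0.020 × √150 = 0.24 and 0.027 × √150 = 0.33. The biases are therefore about 0.4 and 4 standard errors.

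**3. Simulations with threshold shapes.** Assumed: true effect 2, about 19 to 20% treated, prescribing and decline both rising below FEV1% 80 and at ages 12 to 19, 200 replicates per setting.

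- One set of strengths at n = 3000: bias -0.23 with SE 0.45 (0.23 / 0.45 = 0.5 SE). With splines and arm-specific outcome models: 0.01 with SE 0.42. At half the curvature: -0.08 and -0.02.
- Another set: bias about -0.35 at n = 1000, 3000 and 8000. Coverage of the 95% interval was 93%, 86% and 73%, against about 93 to 94% with splines by arm. The largest weighted standardised mean difference for age and FEV1% averaged about 0.08, below the conventional 0.1 flag, so a check on means can miss this. At half the curvature, bias was about -0.03 to -0.08.
- A further set of assumed shapes at n = 3000: bias -0.10 to -0.14 with SE about 0.5 (0.2 to 0.3 SE), nearly removed by splines.

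**4. Cost of flexibility.** Counting the Covariates list with hypertonic saline and inhaled antibiotics as separate indicators gives 4 continuous terms, 3 terms for intravenous days, 8 indicators and an intercept: 16 parameters. A k-knot restricted cubic spline adds k − 2 terms per variable, so the total is 20 with 3 knots, 24 with 4 and 28 with 5. An arm-specific outcome model must estimate all of these in the treated group alone. At n = 400 with 13 to 18% treated (52 to 72 people), 4-knot arm-specific models had coverage of only 82%. With 3 knots and a pooled outcome model, the cost was close to nil at n = 400, 1000 and 3000. With no curvature at n = 3000, standard errors were 0.462 (linear) and 0.459 (spline).

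**The case against.** Several stronger readings are tempting, and the documents do not support them.

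- A reader might infer that a single non-linearity breaks both models and that double robustness is lost. The treatment and outcome regressions are different functions, and curvature in one does not imply curvature in the other. The single-model rows in the table show the property working. The protocol's statement of it is correct, and using the same confounders in both models is needed for confounding control.
- A reader might fault both models for having no treatment interaction. Treatment is the dependent variable of the propensity model, so this can concern only equation 4. The omission is harmless if the propensity model is right, and neither the estimand nor equation 5 imposes a constant effect.
- A reader might infer that the bias hides a benefit. The sign comes from the assumed shapes, and other shapes would reverse it.

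The case for leaving the plan alone has some weight. Only four confounders are affected, linear main effects are a conventional choice, and weighted balance will be checked. The target trial's own imprecision also dominates the comparison with it. Assuming an SD of 8 to 12 points, its standard error with 40 and 42 people is SD × √(1/40 + 1/42) = 1.8 to 2.7, so a shift of 0.23 moves the standardised difference by at most 0.09 to 0.13 against 1.96.

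What stands of this is that the expected effect on that criterion is small under threshold shapes. It does not remove the concern about the emulated estimate and its interval. Knot placement can be left to a fuller plan, but linear terms are what this protocol specifies.

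**Conclusion.** The point holds as a conditional weakness. Both working models are pre-set as linear main effects of the same C. If one of the four continuous confounders acts non-linearly on both prescribing and FEV1% at time 1, both are misspecified and the reason given for choosing AIPTW offers no protection.

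Whether that happens, in which direction and by how much cannot be known from the protocol. Under the assumed threshold shapes the bias was modest, about 0.1 to 0.35 points, or 0.2 to 0.5 standard errors where n was 3000 and a standard error was recorded. It approached 1.4 points only with strong assumed quadratic curvature in both models, and 1.7 when an interaction was also omitted. The change is worth making because a low-order spline is cheap, not because a large bias has been shown.

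**What to change.** In equations 3 and 4, and in equation 6 where it reuses C, enter age, baseline FEV1%, BMI z-score and FEV1% decline as restricted cubic splines: 3 knots by default, 4 to 5 where the number treated allows. Fit the outcome model separately by arm only where the treated group is large enough for the number of parameters; otherwise keep the pooled model. Fix the rule for choosing between these before outcomes are analysed. Report the all-linear version as a sensitivity analysis.

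The cost is revised wording, a few lines of code and 4 extra parameters per model at 3 knots. No new data are needed. The main risk is understated standard errors if arm-specific models with 4 to 5 knots are used in emulations with few treated people, and the default above is set to avoid it.

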##### Additional analysis in the UK Emulated Trial making use of data on treatment prescription dates

A limitation of this approach is that it assumes individuals with A=1 at time 1 have been taking azithromycin for the past 12 months. Realistically, individuals may initiate treatment with azithromycin at any time between time 0 and time 1. For the most recent time period, we can conduct a second analysis using the UK data and making use of data on treatment prescription dates.

In this second analysis, AIPTW is used as above, but the outcome model used previously (equation 3) is modified to include a variable indicating time and an interaction term between time and treatment. We define a new time variable, $t^{*}$, which measures time in months. For treated individuals, $t^{*}=0$ on the first date they are prescribed azithromycin after the index visit. For control individuals, $t^{*}=0$ for the date of the index visit. We let $Y_{t^{*}=12}$ denote FEV_1_% measured on the day of the annual review after $t^{*}=0$ and closest in time to $t^{*}=12.$ Note that this accommodates the fact that annual review visits do not always take place exactly 12 months apart. The outcome model will then be defined as:

(6)
$$Y_{t^{*}=12}=\delta_{0}+\delta_{A}A+\gamma_{c}C+\delta_{t^{*}}t^{*}+\delta_{At^{*}}At^{*}+\epsilon$$

After fitting this model, we set $t^{*}=12$ to obtain the relevant expected outcomes.

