### Sample size

The target trial included 82 individuals (40 in the treated group and 42 in the placebo group). The authors note in their discussion that it is possible the study was not adequately powered to detect significant differences in FEV_1_%.

We have not performed sample size calculations for the emulated trials, and there is some debate as to whether sample size calculations are needed in studies using observational data.^33^,^35^ We plan to use all the available data in the UK CF Registry or US CF Registry and expect much larger sample sizes than were used in the target trial.

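### Equation 5, the printed AIPTW estimator for the primary result, carries an undefined subscript in its augmentation term; read literally, it does not estimate the treatment effect

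*Protocol article*

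**What the plan says.** The Notation section defines treatment as binary: "Let A denote an indicator variable for treatment strategy (A=0 indicates no prescription of azithromycin and A=1 indicates prescription of azithromycin"). It does not define `a_i`. The Main analysis section names the method, "We use augmented inverse-probability-of-treatment weighting (AIPTW) to control for potential confounding by C", and gives double robustness as the reason for choosing it. Equation 3 is the propensity model and equation 4 the linear outcome model.

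Equation 5 combines the two. Its weighted first term uses `I(A_i=a)`, with a the fixed strategy whose mean is being estimated. Its augmentation fraction reads, in source notation and cut before the closing brackets, "I(A_{i}=a_{i})-\hat{P}(A_{i}=a|C_{i})}{\hat{P}(A_{i}=a|C_{i". Within that one fraction the indicator carries `a_i` while both probabilities carry `a`. The next sentence explains where `P(A_i=a_i|C_i)` comes from, although the equation contains only `P(A_i=a|C_i)`. The text then says "The estimator in equation 5 can be used to estimate" both arm means, and that "the difference between these two expectations is an estimate of the average treatment effect in the population".

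The additional UK analysis with prescription dates says that it modifies "the outcome model used previously (equation 3"). Equation 3 is the propensity model; the outcome model is equation 4.

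**The concern.** In AIPTW the augmentation term has mean zero when the propensity model is right, because `I(A_i=a)` averages to `P(A_i=a|C_i)` given the covariates. That property gives the estimator its double robustness. In ordinary notation `a_i` is the observed value of `A_i`. On that reading `I(A_i=a_i)` compares a person's treatment with itself, equals 1 for everyone, and the mean-zero property fails.

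The place matters. This is the formula for the primary outcome, it applies to both registries, and Table 3 lists five registry-period combinations (three UK, two US). The continuous secondary outcomes are analysed the same way. The Rationale section says that the article contains the statistical analysis plan and follows a template aimed at reproducibility, so someone repeating the work could reasonably code from it.

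**Working it through.** **Inputs.** The estimator, the binary treatment and the estimand E{Y1(1)} − E{Y1(0)} come from the Notation, Causal estimand and Main analysis sections. The protocol gives no treated share and no expected mean FEV1%; its Sample size section states "We have not performed sample size calculations for the emulated trials". The means, effects and treated shares below are therefore assumptions. There is no figure in the plan to reproduce.

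**Algebra.** Write P_a = P(A=a|C) and m_a = E(Y1|A=a,C), and suppose both models are correct.

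- First term: E[I(A=a)·Y1/P_a] = E[m_a].
- Augmentation with `I(A_i=a)`: E[(I(A=a) − P_a)/P_a · m_a] = 0. The estimator converges to E[m_a], as it should.
- Augmentation with the indicator fixed at 1: E[(1 − P_a)/P_a · m_a] = E[m_a(1/P_a − 1)].
- Printed estimator: E[m_a] − E[m_a(1/P_a − 1)] = E[m_a(2 − 1/P_a)].

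The printed form therefore misses its target even when both working models are right.

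**Illustration with constant propensity.** Assume a treated share p, a treated mean of 82 and a control mean of 80 (true effect +2). The printed limits are 82(2 − 1/p) for the treated arm and 80(2 − 1/(1 − p)) for the control arm.

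| p | Treated arm | Control arm | Printed difference |
|---|---|---|---|
| 0.20 | 82 × (−3) = −246 | 80 × 0.75 = 60 | −306 |
| 0.25 | 82 × (−2) = −164 | 80 × 0.667 = 53.3 | −217 |
| 0.30 | 82 × (−1.333) = −109.3 | 80 × 0.571 = 45.7 | −155 |
| 0.40 | 82 × (−0.5) = −41 | 80 × 0.333 = 26.7 | −68 |
| 0.50 | 0 | 0 | 0 |

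The difference follows the treated share, not the effect.

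**Illustration with confounding.** This used 200 simulated data sets of 2,000 people, with one confounder, a control mean of 80, residual SD 10, a true effect of 2, and both models correctly specified.

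- Treated share about 0.2: mean estimate 2.06 with `I(A_i=a)`; −368 as printed.
- Treated share about 0.5: mean estimate 1.92 with `I(A_i=a)`; −10.1 as printed, with arm means of −16.4 and −6.3.

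Changing the one subscript brings the estimate back close to the assumed truth in both settings.

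**The case against.** The strongest reply is that `a_i` is undefined, so an indicator that always equals 1 is a reading and not something the document states. The sentence after equation 5 uses `a_i` where the equation has `a`, which suggests that the two are meant as the same symbol. With `a_i` = `a` the equation is standard AIPTW. The method name, the double-robustness statement, the first term, the denominators and the conditioning in the outcome prediction all agree with that. This stands: the choice of method is sound, and the slip is one of notation.

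A reader might infer that the primary estimates in all five emulations will be wrong. The documents do not support that. Nothing says the estimator will be coded by hand from equation 5, and standard AIPTW software would not reproduce the slip. A reader might also infer that the standard errors inherit the error. The protocol bases them on the efficient influence function with its own citation and does not derive them from the printed expression.

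It is also fair to say that the error would reveal itself. Negative or zero mean FEV1% is impossible. At a treated share of exactly 0.5 the difference of 0 looks plausible, but both arm means are 0 as well.

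The equation 3 reference is harmless in practice, since the text calls it the outcome model and equation 6 is written out in full. It is still the wrong number.

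What survives is that the formula printed for the primary result does not match its description unless the reader silently corrects it.

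**Conclusion.** Wrong as written, and minor. Equation 5 needs `I(A_i=a)` in its augmentation term. If `a_i` is read as the person's own treatment, the limit is E[m_a(2 − 1/P_a)], which is neither consistent for the arm mean nor doubly robust. The algebra rests on that reading and on both working models being correct. The range of −306 to 0 in place of +2 also rests on assumed means of 82 and 80 and a constant propensity of 0.2 to 0.5. It shows how the printed form behaves and does not predict the study's results. The practical risk is confined to code written directly from the equation. The estimand, the working models and the choice of AIPTW are untouched.

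**What to change.** 1. In equation 5, replace `I(A_i=a_i)` with `I(A_i=a)` in the augmentation term.
2. In the sentence below it, write `P(A_i=a|C_i)` in place of `P(A_i=a_i|C_i)`.
3. In the additional UK analysis with prescription dates, cite equation 4, not equation 3, as the outcome model that becomes equation 6.

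The cost is two subscripts and one cross-reference, with no change to data, design or planned method.
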